## Results

The TELESAGE study is sponsored by Sanofi (Gentilly, France). A primary completion date is expected in June 2018, and publication of results is expected within 6 months of work completion.

## Discussion

### Study Rationale

The DIABEO telemedicine system has previously showed superiority to usual follow-up in improving HbA_1c_ in patients with poorly controlled diabetes [9]. The current TELESAGE study is expected to confirm this result in a larger sample of diabetic patients and real-life conditions. Moreover, the TELESAGE study will validate the present physician/nurse delegation protocol.

The TELEDIAB 1 study showed that the DIABEO telemedicine system improves HbA_1c_ without requiring more medical time and providing far more services compared to usual care [9]. In this respect, the TELESAGE study will test the efficacy of a closer follow-up by the nursing staff as compared with the previous physician-assisted telemedicine system.

Usually, a T1DM or T2DM patient undergoing a basal-bolus insulin regimen sees their diabetologist every 3 to 6 months. At the hospital, the patient can also be monitored by a nurse for therapeutic education (whether or not the patient is hospitalized), which can help in difficult moments (eg, hospitalization following a serious adverse event or during a major treatment switch such as from injectable treatment to insulin pump treatment).

The DIABEO telemedicine service has several strengths. Patient data is daily analyzed by the DIABEO system to fight against glycemic instability and complications. In very serious cases, analysis of these data allows triggering nursing actions and/or physician actions. Nursing delegation also allows more availability to receive patients’ calls and respond to daily issues. Continuity and continuity of care is thus organized from Monday to Saturday from 8am to 8pm.

If positive results are obtained, TELESAGE will clearly demonstrate that the DIABEO telemedicine service could be an integral part of the ambulatory care of an insulin-treated patient.

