### Randomization

Patient randomization is automatically done by using the electronic case report form software. A first randomization step allocates the study arms at the regional level: (i) six regions including patients in arms 1 and 2 (Aquitaine, Île-de-France, Lorraine, Nord-Pas-de-Calais, Rhône-Alpes, and Languedoc-Roussillon) and (ii) six other regions including patients in arms 1 and 3 (Alsace, Franche-Comté, Lower Normandy, Midi-Pyrénées, Pays de la Loire, and Provence-Alpes-Côte d'Azur). Then, within each region the patients are further randomized between the two groups (done at patients’ inclusion, between arms 1 and 2 or between arms 1 and 3). The distribution by center was 1:2 (ie, 1 patient of arm 1 for 2 patients of arms 2 or 3).

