### Outcome Measures

The primary outcome measure of this study is to investigate the effect of a 12-month follow-up with the DIABEO system (software + physicians’ telemedicine, or software + nursing telemonitoring, and teleconsultations by diabetologist’s task delegation) versus usual follow-up in terms of improvement of glycemic control (HbA_1c_ levels) in T1DM or T2DM patients poorly controlled by a basal-bolus insulin regimen. HbA_1c_ high performance liquid chromatography assays are performed at qualified medical biology laboratories and then reported by participants to investigators. Secondary outcome measures are to compare groups for: HbA_1c_ levels, percent of responder patients (HbA_1c_ <7.5% or HbA_1c_ reduction ≥1%) and severe hypoglycemia at 6, 12 and 24 months, as well as for quality of life and satisfaction (of patients and physicians) at 12 and 24 months. Severe hypoglycemia was defined as requiring third-party assistance. Quality of life was assessed by a specific questionnaire, derived from the EuroQol five dimension scale (EQ-5D) questionnaire [11]. For participants of arms 2 and 3, satisfaction with the DIABEO telemedicine system is evaluated at each center, with a patient’s self-assessed specific questionnaire.

Other secondary, medico-economic outcome measures, have been designed to compare groups at 12 and 24 months for resource consumption and health insurance costs (including overall costs of diabetes and complications, and costs per point of HbA_1c_ reduction and for severe hypoglycemia avoided). If the study demonstrates an overall statistically significant effect, subgroups analyses will be conducted to identify the patients’ profiles with optimal costs consequences and cost-effectiveness ratios.

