### Statistical Analysis

#### Patient Population Size

The initial sample size to detect a ≥0.5% difference in HbA_1c_ from baseline to month 12 was estimated using a standard deviation of 1.2%, a rate of not evaluable patients of 15% and an intracluster correlation coefficient of .005 (a measure degree of homogeneity within the same region). This calculation predicted an initial sample size of 696 patients to achieve ≥90% power in detecting a difference in outcome.

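### The nurse-versus-physician comparison promised in the Discussion is between regions or indirect through arm 1, and should be governed by a region-respecting analysis and labelled exploratory

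*Protocol article*

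**What the plan says.** All places are in the Protocol article.

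- **Study Rationale (Discussion):** the trial "will test the efficacy of a closer follow-up by the nursing staff as compared with the previous physician-assisted telemedicine system".
- **Randomization:** twelve regions were allocated by a first randomisation, six to arms 1 and 2 and six to arms 1 and 3. Patients are then randomised within region "between arms 1 and 2 or between arms 1 and 3", one control to two on the active service.
- **Outcome Measures:** the primary outcome sets DIABEO, in either form, against usual follow-up. Secondary outcomes compare groups, without naming the pairs. "For participants of arms 2 and 3, satisfaction with the DIABEO telemedicine system is evaluated at each center"; Table 1 likewise marks this questionnaire for groups 2 and 3 only.
- **Patient Population Size:** the calculation allows for "an intracluster correlation coefficient of .005 (a measure degree of homogeneity within the same region").
- **Data Analysis:** ANCOVA for the primary end point; ANCOVA, chi-square and Fisher exact tests for the rest. An analysis adjusted for center and region is planned as confirmatory.
- **Limitations:** only the open-label design and the reporting bias it allows.

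**The concern.** The Discussion announces a head-to-head result for the two services, but no patient is ever randomised between them. The units randomised between arm 2 and arm 3 are 12 regions. A patient-level test that ignores region gives that contrast the precision of a patient-randomised one. It also lets differences between regions in case mix, center practice or recruitment pass as an effect of nurse delegation.

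At stake is a statement that the nurse service is better than, or as good as, the physician service. The article does not warn the reader that this contrast has a weaker basis than either comparison with usual follow-up.

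**Working it through.** **Inputs.** From Patient Population Size: target difference 0.5% in HbA1c at month 12; SD 1.2%; 15% of patients not evaluable; intracluster correlation (ICC) .005 for region; and, as the result, "an initial sample size of 696 patients to achieve ≥90% power in detecting a difference in outcome". From Randomization: 6 + 6 regions, 1:2 allocation. Assumed: the two sets of regions and the regions within them are equal in size, and SD 1.2 applies to the analysed outcome.

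**The plan's own figure.** Alpha and the multiplicity rule are not given in the article, so they are varied here. N = 3 × n × [1 + (m − 1) × .005] / 0.85, where n is the per-arm number for 0.5%, SD 1.2 and 90% power, and m is the cluster size. The per-arm figure is rounded up.

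- Two-sided alpha 0.05/3: n = 156. With m = 58 (696/12), N = 708; with m = 49.3 evaluable, N = 684.
- Two-sided alpha 0.05: n = 122. With m = 116 (696/6), N = 681; with m = 58, N = 555.

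The stated 696 is thus reproduced within 3% under more than one reading. The match does not show which contrasts were sized.

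**Evaluable numbers.** Each set of regions has 696/2 = 348 patients: 116 controls and 232 on the service. At 85% evaluable this is 98.6 and 197.2. Arms 2 and 3 together have 2 × 197.2 ≈ 394.

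**Direct contrast, region ignored.**

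- Reported SE = 1.2 × √(2/197.2) = 0.121.
- Patients per region and arm = 197.2/6 = 32.9. Design effect = 1 + 31.9 × .005 = 1.16.
- True SE = 0.121 × √1.16 = 0.130, so the SE is understated by about 7%.
- Actual error of a nominal 5% test = 2 × [1 − Φ(1.96/√1.16)] = 2 × [1 − Φ(1.82)] ≈ 6.9%.

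| ICC | Design effect | Type I error, formula | Type I error, 20,000 simulated trials |
|---|---|---|---|
| .005 (article) | 1.16 | 6.9% | 6.7% |
| .02 (assumed) | 1.64 | 12.6% | 12.4% |
| .05 (assumed) | 2.59 | 22.4% | 22.6% |

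**Contrast through arm 1, fixed region effects.** This is (arm 3 − arm 1 in its regions) − (arm 2 − arm 1 in its regions).

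- Estimability: with 12 region columns and 2 arm columns the design matrix has rank 14 of 14. Without arm 1 the rank is 12 and the contrast cannot be estimated.
- SE = 1.2 × √[2 × (1/98.6 + 1/197.2)] = 0.209, which is √3 = 1.73 times the naive SE.
- 95% CI half-width = 1.96 × 0.209 = 0.41.
- Power for 0.5% = Φ(0.5/0.209 − 1.96) ≈ 67%. The difference detectable with 90% power is 0.68%.
- Simulated type I error is 4.9% to 5.3% for ICCs from 0 to .05.

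**Direct contrast at cluster level (t, 10 df), ICC .005.** Power ≈ Φ(0.5/0.130 − 2.228) ≈ 95%. It falls to about 84% at ICC .02 and 63% at .05, both assumed.

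**DIABEO satisfaction.** Arm 1 has no such measure, so there is no bridge. Arm 3 versus arm 2 is purely between regions.

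**The case against.** The strongest reply is that the article anticipates regional clustering. It carries a region-level ICC in the sample size and plans an analysis adjusted for center and region. With arm 1 in the model, that analysis gives essentially the protected contrast. Nor does the article specify an arm 3 versus arm 2 ANCOVA without region; covariates and contrasts may be set out in a full protocol or analysis plan that is not shown. All of this stands. What remains is that the article states the comparison outright, gives region a role only in a confirmatory analysis, and does not tell the reader that the contrast is not patient-randomised.

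A reader might infer several stronger points that the article does not support:

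- **That the HbA1c contrast is fully confounded with region.** It is not. Regions were themselves randomised, and arm 1 is in all twelve, so the contrast is estimable. Only the satisfaction comparison lacks a bridge.
- **That the error rate is 12% or 22%.** Those figures need ICCs four and ten times the planned one, and nothing in the article supports them.
- **That 0.24% (0.91 − 0.67 from TELEDIAB 1) is the difference to power for.** Those two figures are for the software with and without teleconsultations, not for nurse against physician delivery.
- **That the intention to validate the delegation protocol depends on this contrast.** It can rest on arm 3 versus arm 1, which is patient-randomised within region.

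**Conclusion.** The point holds in limited form. The Discussion promises a test that the design supports only between 12 regions or indirectly through arm 1, and Limitations is silent on this. At the article's own ICC the harm from ignoring region is modest: SE 0.121 instead of 0.130, and about 6.9% error instead of 5%. It grows if the ICC was set too low.

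The two valid routes differ in strength. The contrast through arm 1 has about 67% power for 0.5%, short of the 90% the trial was sized for. The direct cluster-level test has about 95% power at ICC .005, but it depends on only 12 regions and on that ICC.

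The figures assume SD 1.2, equal regions and no region-by-treatment variation. Fixed region effects do not remove such variation, so 0.209 is a best case. The bridge also weakens at 24 months, because controls may take up the software after month 12 (Study Design). The primary comparisons with usual follow-up have concurrent controls in the same regions and are not affected.

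**What to change.** 1. For any arm 3 versus arm 2 comparison, make the region-respecting analysis the governing one: the region-adjusted contrast through arm 1, with a 95% CI, labelled exploratory. As sensitivity, give a direct contrast with region as a random effect and small-sample degrees of freedom for 12 clusters.
2. Report DIABEO satisfaction by arm descriptively, or with a region-level analysis.
3. Reword Study Rationale to say that the trial estimates each service against usual follow-up, and that nurse versus physician is an exploratory between-region or indirect contrast. Add this to Limitations.

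No change to design or data collection is needed; the work is wording and one model contrast. The downside is a wider interval and a weaker claim for nurse versus physician delivery.

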### Limitations

Given the impossibility of double-blind assessment of open-label intervention versus usual follow-up, the effects of report bias cannot be eliminated.

## Abbreviations

ANCOVA: analysis of covariance
ANSM: Agence Nationale de Sécurité du Médicament (National Agency for Drug Safety)
BMS: Bristol-Myers Squibb
CERITD: Centre d'Étude et de Recherche pour l'Intensification du Traitement du Diabète
CPP: Comité de Protection des Personnes (Committee for People Protection)
EQ-5D: EuroQol five dimension scale
GSK: GlaxoSmithKline
HAS: Haute Autorité de Santé (France)
HbA_1c_: hemoglobin A_1c_
MSD: Merck Sharp and Dohme
SMPG: self-monitoring plasma glucose
T1DM: type 1 diabetes mellitus
T2DM: type 2 diabetes mellitus
TELESAGE: Suivi à Grande Échelle d’une cohorte de diabétiques de type 1 et de type 2 sous schéma insulinique basal bolus par la TELEmédecine
